### 6.2.1 Vaccine Labeling

1. Each dose of vaccine is packaged separately and the vaccine number is stuck onto.
2. After the vaccine is put into use, the initials of the participant and the vaccination date shall be filled on the outer package.

### Clinical Trial Labeling Illustration

Outer Packaging Box Label

|                                                  |                          |           |           |           |
|--------------------------------------------------|--------------------------|-----------|-----------|-----------|
| Recombinant COVID-19 Vaccine (NVSI-06-09) |                          |           |           |           |
| For Clinical Research Use Only            |                          |           |           |           |
| Vaccine Number: AExxxx                    |                          |           |           |           |
| Initials:                                 | Vaccination Date: | YY | MM | DD |
| Storage at 2-8°C, 0.5mL/dose              |                          |           |           |           |
| Batch Number:                             |                          |           |           |           |

Vaccine Label:

**CONFIDENTIAL**

**Recombinant COVID-19 Vaccine (NVSI-06-09)****(For Clinical Research Use Only)**

Vaccine Number: AExxxx

Batch Number: XXXX

### 6.3 Vaccine Storage and Transportation

Vaccines should be stored and transported at 2 ~ 8 °C away from light to prevent freezing. The temperature during vaccine transportation and storage shall be dynamically monitored and recorded. If the storage and transportation temperature conditions exceed the specified range, the on-site investigators should immediately contact the personnel of the responsible clinical institutions and the Sponsors to decide whether the vaccine can be used.

The management of receiving, keeping, formulation, recycling, returning/destroying of the investigational vaccine shall conform to the requirements of relevant laws and regulations.

#### 6.3.1 Vaccine Transportation

The whole process of vaccine management should meet the cold chain requirements, and there should be vaccine transportation and storage conditions that meet the requirements of the protocol. During the vaccine transportation, there should be a delivery note and temperature monitoring. Upon arrival, the packaging condition and unpacking temperature should be recorded. After the recipient receives the vaccines, the delivery note should be signed, faxed, or copied to the sender. Both parties should keep the delivery note properly.

#### 6.3.2 Vaccine Storage and Distribution

The investigational vaccines should be kept in a separate area, locked in a dedicated cabinet and managed by dedicated personnel. Vaccine recipients must verify and record the batch number, expiry date and delivery status of vaccines, create worksheets for vaccine handover, registration, use and recycle, fill in as required, and keep them in the working logs. The trial vaccine shall not be used in the non-clinical trial population.

**CONFIDENTIAL**

### 6.3.3 Vaccine Records

***Vaccine handover records:*** The Sponsor will provide investigational vaccines, control vaccines (placebo) and vaccine handover sheet, and the investigator will verify the name, batch number and quantity of the vaccine upon receiving.

***Vaccine registration and use records:*** the investigator shall establish vaccine registration and use records and distribute investigational vaccine and control vaccines according to the number of people in the observation groups.

***Vaccine recycle record:*** The abandoned, expired and remaining vaccines in this trial are returned to the Sponsor. Sponsor receives vaccines and verifies the batch number and quantity of vaccines, fills in the vaccine handover form, and makes relevant records, which are signed by the vaccine manager and Sponsor representatives.

### 6.4 Administration and Immunization Schedule

***Route of Administration:*** lateral deltoid muscle of either upper arm, intramuscular injection.

***Vaccination Procedure:*** Among the population who had completed two/three doses of inactivated COVID-19 vaccines according to the 0 and 21 days (+7 days) immunization schedule, one dose of Recombinant COVID-19 Vaccine (NYSI-06-09) or inactivated COVID-19 vaccine (Vero cell) will be inoculated at  $\geq 6$  months for booster immunization.

## 7. STUDY WORKFLOW AND VISITING METHOD

### 7.1 Schedule of Visits

Table 5 lists the assessment items and procedures according to the phase of the clinical studies and visits.

### 7.2 Study Procedure

CONFIDENTIAL

### **7.2.1 Screening Period/Baseline Period and Vaccination Procedure (D0)**

The first visit was conducted according to the following procedure and evaluation processes.

#### **Recruitment:**

The investigators will jointly publicize this clinical trial recruitment notice to qualified volunteers/guardians, examined, and approved by the Ethics Committee, with local medical staff, and recruit and register candidate participants based on the principle of voluntary participation. During the study, the recruitment should be adjusted in real-time progress, to ensure that the gender and age of the participants are relatively balanced.

#### **Informed Consent:**

Informed consent refers to the voluntary participation of participants in clinical studies. Before the commencement of any test-related procedures (any genetics-related sample collection, testing, etc.), written informed consent must be obtained from the participant.

After arriving at the research site, the participants first give informed consent. The investigators inform the participants of the informed consent form of this clinical trial orally and in writing, including study purpose, procedure, duration, risks and benefits, etc. Under the condition of voluntary participation, the participants and research doctors signed an informed consent form together. The informed consent form shall be made in duplicate, the guardian or principal of the volunteer shall keep a copy, and the original shall be kept at the study site.

Collect contact information (address, e-mail, landline, mobile phone numbers, etc., if applicable) of participants and their families.

#### **Physical Examination, Inclusion/Exclusion Criteria:**

Volunteers who signed the informed consent were given height, weight, body temperature, blood pressure (aged 18 and above), cardiopulmonary auscultation, skin examination. Within 10 minutes before the temperature test, the participants are forbidden to eat or drink anything hot or cold, or smoke.

According to the "inclusion criteria" and "exclusion criteria", the investigators inquire, understand,

**CONFIDENTIAL**

and check the vaccination records of the participants, that is, the past medical history, and judged whether the participants should be enrolled in this clinical trial according to the inquiry results.

**Study Number Assignment:**

Eligible participants are assigned unique study numbers in sequence. Once the study number is assigned, it cannot be reassigned to other participants.

**Blood Sample Collection before Vaccination:**

Women of childbearing age (from menarche to menopause) need to collect about 2ml urine samples for urine pregnancy tests before vaccination.

About 12.5 ml of blood samples are collected on an empty stomach for SARS-CoV-2 antibody detection after recruitment.

Nasopharyngeal swabs are collected for PCR detection to establish antibody baseline and PCR baseline for booster inoculation. After sample collection, the participants can enter the following process.

**Vaccination:**

Participants can be vaccinated after sample collection. Before vaccination, it is necessary to check the information of participants and the investigational vaccines, obtain vaccines with corresponding numbers and open the outer package. After the vaccine label and outer package label are checked, fill in the initials of the vaccinee's name and vaccination date on the label of the outer package.

Vaccination site is at the lateral deltoid muscle of the upper arm, in principle, the non-habitual arm of the participant.

During vaccination, the investigational vaccine and control vaccine should be kept at 2 ~ 8 °C (the temperature should be monitored and recorded every 1 hour), and it should take no more than 30 minutes from the time the vaccine is taken out of the heat preservation container to the

**CONFIDENTIAL**

completion of vaccination.

During vaccination, in case of abnormal colour, damage, insufficient loading or precipitation, it is necessary to stop vaccination immediately, report to the Sponsor, auditor and on-site person in charge, discard the original vaccine according to the procedure after confirming the damage of the vaccine, and obtain a new vaccine number in the system by the distribution principle of the central randomized system after approval. Record the injection site (right arm or left arm) and vaccination information.

### **On-site Medical Observation:**

Observe the immediate adverse reactions 30 minutes after vaccination. Doctors explain on-site adverse reaction judgment, measurement methods, recording methods, precautions, reporting methods, etc. Diary cards, rulers and thermometers are distributed and train participants how to use thermometers correctly, observe adverse events and fill in diary cards within 0-7 days after vaccination, and inform them of the time to make an appointment to return the diary cards (return the completed diary cards on 28th day after vaccination).

Ask the participants to try to take temperature measurements at the same time every day within 7 days after vaccination. Before leaving the study site, the vaccination site and body temperature of the participants should be checked, and the observed adverse events should be evaluated and recorded in the electronic system.

Inform the participants that they should take the initiative to provide any adverse reactions and accompanying medication. If there is any reaction after vaccination, it is necessary to inform the study centre in time. PI or qualified SI will evaluate them, provide the participants with the correct response plan, and ask them to return to the clinic for immediate evaluation if necessary.

## **7.3 Safety Observation and Follow-up**

### **7.3.1 Safety Observation**

1. Observe the site for 30 minutes after vaccination to collect local and systemic adverse events.
2. Telephone follow-up once in 6-24 hours after vaccination, within 1-3 days and 4-7 days

**CONFIDENTIAL**

respectively, the participants were followed-up by telephone and guided to observe the adverse events correctly and fill in the diary card.

3. On the 14th day after vaccination, the investigator reviews the filling of the diary card during this period and re-collect the diary card.
4. On the 8th -28th day after vaccination, the investigator uses telephone follow-up once a week, combined with an active report of the participants to monitor the safety.
5. When it is known that the participant has adverse reactions/events of Grade 3 or above, a face-to-face visit should take place within 24 hours.
6. SAEs and AESIs are observed from the first dose to 12 months after the full course of vaccination via monthly telephone follow-up calls and self-reports from the participants.
7. Participants should contact the doctors on informed consent form/diary card immediately if developed any COVID-19 like symptoms.

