**Safety Observation:**

The participants will be observed at the study site for 30 minutes after immunization, and local and systemic adverse events will be actively collected and recorded on the diary cards within 0-7 days. Perform one safety follow-up per week to collect AEs and record them in the follow-up system. Serious adverse events (SAEs) will be monitored within 12 months after immunization and follow-up, recorded and report according to requirements.

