**Abbreviations: N: number, D: days, M, months.**

a Blood collection window at D14 and D28 is +10 days

b Blood collection window at 3M, 6M, 9M, 12M is +30 days.

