### 4.3. Study Endpoint

**CONFIDENTIAL**

**Primary Endpoints:**

1. GMT and the 4-fold rise rate of anti-omicron neutralizing antibody 14 days after a single dose of the booster vaccine in adults  $\geq 18$  years of age.
2. The incidence and severity of any adverse reactions/events within 30 minutes after vaccination;
3. The incidence and severity of solicited adverse reactions/events within 0-7 days after vaccination;
4. The incidence and severity of unsolicited adverse reactions/events within 8-30 days after vaccination;
5. The incidence of SAE and AESI observed after vaccination and up to 12 months after full course of immunization.

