###### (2) Adverse events collected in 8-28 days

**CONFIDENTIAL**

Any medical events, such as acute diseases and accidental injuries occurred during 8~28 days in clinical studies.

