| Visit (window +/-days)
The subsequent visit is postponed accordingly | 0d                                                                                      | -2d                                                                                     | -3d                                                                                     | + 10d                                                                                    | +7d                                                                                        | + 10d                                                                                      | +10d                                                                                               | + 30d                                                                                              | +10d                                                                                               | +10d                                                                                               | + 30d                                                                                              | + 30d                                                                                              | + 30d                                                                                               |

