| Telephone follow-up after vaccination                                   | ✓                                                                                       | ✓                                                                                       | ✓                                                                                       |                                                                                          | ✓                                                                                          |                                                                                            | ✓                                                                                                  | ✓                                                                                                  | ✓                                                                                                  | ✓                                                                                                  | ✓                                                                                                  |                                                                                                    |                                                                                                     |

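### Section 7.3.1 requires weekly safety calls on days 8-28, but the Schedule of Events lists one call and ties the other two contacts to +10-day blood windows

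*Protocol*

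**What the plan says.** **Text.** Section 7.3.1 item 4 says that for days 8-28 "the investigator uses telephone follow-up once a week, combined with an active report of the participants to monitor the safety". The Safety Observation paragraph of section 4.2 reads "Perform one safety follow-up per week to collect AEs and record them in the follow-up system"; it does not say that the contact must be by telephone.

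**Schedule of Events (section 7.4).** The row "Telephone follow-up after vaccination" is ticked at V1, V2, V3, V5 and V7 to V11. It is blank at V4 (D14), V6 (D28), V12 and V13. The window row gives V3 minus 3 days, V4 plus 10, V5 plus 7 and V6 plus 10, with the note "The subsequent visit is postponed accordingly". The V4 and V6 windows match footnote a of Tables 1 and 2: "Blood collection window at D14 and D28 is +10 days".

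**What is counted.** Primary endpoint 4 in section 4.3 is "The incidence and severity of unsolicited adverse reactions/events within 8-30 days after vaccination". Section 4.5.1 (2) collects events that "occurred during 8~28 days in clinical studies". The second primary objective concerns safety at 28 days.

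**Diary card.** The Synopsis (Safety Observation) and section 7.6 have days 0-28 recorded on the card. Sections 4.2 and 7.2.1 have days 0-7. Section 7.3.1 item 3 and footnote 4 of the Schedule collect the card at D14; section 7.2.1 has it returned on day 28.

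**The concern.** A site works from the Schedule. If the Schedule shows one call where the text requires one each week, and the remaining contacts move with the blood draw, a site can keep every Schedule window and still breach item 4 without any visit-window deviation showing.

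At stake is the capture of unsolicited events, a primary safety endpoint. The interval over which a participant is asked to recall events would depend on when blood happened to be taken, and would differ between participants. Mild, short events are the ones most likely to be lost over a long interval, so observed incidence would tend to be too low.

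**Working it through.** The protocol states no figure for the interval between contacts, so there is none to reproduce. The check sets the two rules side by side and takes the longest interval that the windows allow.

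**1. Number of calls in days 8-28**
- Item 4: days 8-28 are 28 - 8 + 1 = 21 days, or three weeks, hence about 3 calls.
- Schedule: 1 call (V5).

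**2. Permitted days, from the window row**

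| Contact | Nominal day | Window | Permitted days |
|---|---|---|---|
| V3, call | D7 | -3 | D4-D7 |
| V4, blood visit | D14 | +10 | D14-D24 |
| V5, call | D21 | +7 | D21-D28 |
| V6, blood visit | D28 | +10 | D28-D38 |

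**3. Longest interval between consecutive contacts** (later day minus earlier day)
- Nominal days: 14 - 7 = 21 - 14 = 28 - 21 = 7 days. Contact is weekly.
- V3 at its earliest, V4 at its latest, V5 on D24 or later: 24 - 4 = 20 days.
- V3 on its nominal day: 24 - 7 = 17 days. V5 on D21 followed by V6 on D38 also gives 38 - 21 = 17.
- Calls only, V3 to V5: 28 - 4 = 24 days.

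**4. Effect of the postponement note.** If later visits shift with a late V4, the V3-to-V4 interval is still 24 - 4 = 20 days. V5 would then be due no earlier than 21 + 10 = D31, so no call at all would fall in days 8-28 or 8-30.

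**5. Part of the interval in which unsolicited events are counted.** Counting starts on day 8; D4-D7 belong to the solicited period. With V4 on D24, days 8-23 have no contact: 23 - 8 + 1 = 16 days.
- Over days 8-28: 16/21 = 76%.
- Over days 8-30 (23 days): 16/23 = 70%.

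**6. What item 4 itself would allow.** Read as one call in each of days 8-14, 15-21 and 22-28, the longest interval between calls is 28 - 15 = 13 days. Read as a call every 7 days, it is 7.

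**7. Direction of any under-reporting.** Suppose a fraction f of events is forgotten equally in both arms, with true incidences p1 and p2. Observed incidences become (1 - f)p1 and (1 - f)p2. The absolute difference shrinks to (1 - f)(p1 - p2), and the risk ratio stays p1/p2 but rests on fewer events. The documents give no value for f.

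**The case against.** The strongest reply is that the text and the Schedule are read together. Item 4 is in force, so a site that left 20 days between contacts would breach it. Item 3 also places the diary review on day 14. On nominal days the Schedule gives a call on D7, a visit on D14, a call on D21 and a visit on D28, which meets section 4.2 in full and departs from item 4 only in the mode of contact. Other safeguards run alongside: participants report events themselves, known events of Grade 3 or above lead to a face-to-face visit within 24 hours, and some passages put days 0-28 on the diary card. Both arms share the same windows under blinding.

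Most of this stands, and it rules out three stronger readings that a reader might infer:
- **That the protocol permits 20 contact-free days while unsolicited events are counted.** It does not. Only the Schedule's windows, taken alone, allow the interval, and only 16 of those days lie in the counting period.
- **That no written record covers the period.** The diary passages conflict; they are not uniformly silent after day 7.
- **That incidence is understated by a particular percentage.** No recall-loss rate is given, and the longest interval applies only to participants at the edges of the windows.

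The reply does not remove the contradiction. The telephone row and item 4 still disagree, and nothing says that a visit may replace a call. A card collected at D14 cannot record later events. Self-report depends on the participant. Section 7.3.2 has events asked about at on-site visits, but a bracket excepting scheduled and unscheduled visits leaves it unclear whether V4 and V6 count.

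**Conclusion.** The point holds as an internal contradiction about how a primary safety endpoint is collected: about three calls under item 4 against one in the Schedule, with the other two contacts governed by laboratory windows. The Schedule alone allows up to 20 days between contacts (17 with V3 on D7), leaving days 8-23 uncovered: 16 of 21 or 16 of 23 days, depending on which stated period applies.

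These are maxima over permitted days, not expected intervals. They assume that the windows are as printed and that V4 and V6 do serve as safety contacts. Any effect on incidence cannot be sized from the documents. With equal loss in both arms it would lower observed incidence and the absolute difference rather than favour one vaccine on the ratio scale. The point should be corrected because the repair is cheap and the endpoint is primary; it does not show that the safety comparison is invalid.

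**What to change.** - In the Schedule of Events, show a safety contact in each of days 8-14, 15-21 and 22-28, with windows counted from vaccination and ending within the same week.
- Keep the +10-day windows for blood collection only, and state that the postponement note does not move the safety contacts.
- State in section 7.3.1 item 4 that an on-site visit in a given week may replace that week's call, and clear up the bracket in section 7.3.2.
- Reconcile the diary-card period (days 0-7 or 0-28) and its return date (D14 or day 28) across the Synopsis, sections 4.2, 7.2.1, 7.3.1 and 7.6, and footnote 4 of the Schedule.
- Use one end day for unsolicited events, since sections 4.3 and 4.5.1 differ.

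The weekly blocks bring the longest interval between contacts down from 20 to 13 days; a rule of every 7 days would be tighter, but the text does not clearly require it. The cost is a table amendment with matching text edits and at most about two further short calls per participant, 2 x 516 = 1,032 in all. Fewer are needed when blood visits fall on time, and the text already promises these contacts.

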|                                         | Total sample size (N)                                                                                                                                                                                                                                                                                                                                                                                                                                  |                    | 516 | SAEs collected up to 12 months following the booster dose via safety visits.                   |                                                                                                                                                                                                                                                                                  |                                                                                                                                                             |
|                                         | Abbreviations: N: number, D: days, M, months.
a Blood collection window at D14 and D28 is +10 days
b Blood collection window at 3M, 6M, 9M, 12M is +30 days.                                                                                                                                                                                                                                                        |                    |     |                                                                                                |                                                                                                                                                                                                                                                                                  |                                                                                                                                                             |

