#### **4.5.4 Adverse Event of Special Interest**

According to the CIOMS VII definition, AESI refers to a class of scientific and medical events (including serious or non-serious) related to investigational vaccines or projects, which require investigators to continuously monitor and quickly communicate with the Sponsor. These events need further study to understand their characteristics; Depending on the nature of the event, the Sponsor also needs to communicate quickly with other relevant parties (such as regulatory authorities). The follow-up period of AESI is 12 months after the full course of immunization. AESI related to this vaccine include:

- Nervous system diseases (generalized convulsions, Guillain-Barre syndrome, acute disseminated encephalomyelitis, aseptic meningitis, general convulsions, peripheral facial paralysis, and loss of smell/ taste)
- Immune system diseases (vaccine-related respiratory diseases increase, anaphylactic shock, and multisystem inflammatory syndrome in children)
- Respiratory diseases (acute respiratory distress syndrome)
- Cardiac system diseases (acute cardiovascular injury including myocarditis, pericarditis, arrhythmia, heart failure, myocardial infarction)
- Blood system damage (thrombocytopenia, coagulation dysfunction including coagulation diseases, thrombosis, thromboembolism, internal/external bleeding, and stroke)
- Kidney system diseases (acute kidney injury)
- Liver system diseases (acute liver injury)
- Skin system diseases (chilblain-like lesions, single organ skin vasculitis, erythema multiforme, and alopecia).

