| Concomitant Medication                                                  | ✓                                                                                       | ✓                                                                                       | ✓                                                                                       | ✓                                                                                        | ✓                                                                                          | ✓                                                                                          | ✓                                                                                                  | ✓                                                                                                  | ✓                                                                                                  | ✓                                                                                                  | ✓                                                                                                  |                                                                                                    |                                                                                                     |

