| Neutralizing Antibody/IgG Test                                          | ✓                                                                                       |                                                                                         |                                                                                         | ✓                                                                                        |                                                                                            | ✓                                                                                          |                                                                                                    | ✓                                                                                                  |                                                                                                    |                                                                                                    | ✓                                                                                                  | ✓                                                                                                  | ✓                                                                                                   |

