## 7.10 Site Close

All participants completed long-term safety observation for 12 months after vaccination and blood collection for 12 months after immunization. Trial sites will be closed and immune persistence evaluation will be initiated only once the following activities have been completed:

1. Completed all study requirements according to the study protocol
2. Locked the database
3. Clarification of data by the statistician (blind audit)
4. Unblinded the necessary study staff to evaluate the safety, immunogenicity and

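### Section 7.3.1 promises monthly SAE/AESI calls to 12 months, but the Schedule of Events has no contact at months 7, 8, 10 or 11 and no telephone tick after month 6

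*Protocol*

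**What the plan says.** The 12-month window is stated consistently. Primary endpoint 5 (section 4.3) is "The incidence of SAE and AESI observed after vaccination and up to 12 months after full course of immunization". Section 4.5.4 agrees: "The follow-up period of AESI is 12 months after the full course of immunization". Section 7.10 makes completed 12-month safety observation a condition of site closure.

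The method of collection is stated in different ways:

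- Section 7.3.1, item 6: SAEs and AESIs are followed to "12 months after the full course of vaccination via monthly telephone follow-up calls and self-reports from the participants".
- Tables 1 and 2: "SAEs collected up to 12 months following the booster dose via safety visits".
- Schedule of Events (section 7.4): visits at 2, 3, 4, 5 and 6 months (V7 to V11), then 9 months (V12) and 12 months (V13). The row "Telephone follow-up after vaccination" is ticked at V1, V2, V3, V5 and V7 to V11, and is blank at V4, V6, V12 and V13.

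**The concern.** Item 6 and the Schedule of Events cannot both be followed after month 6. Item 6 calls for a telephone contact every month; the schedule has no place to record one in four of the last six months. Sites usually work from the schedule table, and electronic case report forms are usually built from it, so the table may be what is carried out.

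The endpoint is an incidence over the whole 12 months and depends on how often participants are asked. Less frequent contact after month 6 means longer recall and more reliance on participants volunteering events. Hospitalised or fatal events are likely to surface anyway. Non-serious AESIs on the section 4.5.4 list, such as alopecia, peripheral facial paralysis or loss of smell or taste, are more easily missed. If some sites follow item 6 and others follow the table, ascertainment would also differ between sites.

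**Working it through.** The protocol states no figure of its own here, so the check is a count of scheduled contacts against the monthly calls in item 6.

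**Inputs.** Visit timing and telephone ticks come from the Schedule of Events. Day numbers and windows (D180, D270 and D360, each +30 days) come from the blood sample numbering rule in section 7.4. The sample size of 516 comes from section 4.2.

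| Month | Scheduled visit | Telephone tick |
|---|---|---|
| 1 | V6 (D28) | no |
| 2 | V7 | yes |
| 3 | V8 | yes |
| 4 | V9 | yes |
| 5 | V10 | yes |
| 6 | V11 | yes |
| 7 | none | – |
| 8 | none | – |
| 9 | V12 | no |
| 10 | none | – |
| 11 | none | – |
| 12 | V13 | no |

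**Contacts.** Item 6 implies 6 monthly contacts in months 7 to 12. The schedule has 2. Months with no contact of any kind: 6 − 2 = 4 (months 7, 8, 10 and 11).

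**Share of the endpoint window affected.** 6/12 = 50%.

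**Interval between contacts after month 6.**

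- Nominal: 270 − 180 = 90 days and 360 − 270 = 90 days.
- Longest with the +30-day window: (270 + 30) − 180 = 120 days and (360 + 30) − 270 = 120 days.
- Under item 6: about 30 days.

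**Calls not listed.** 4 × 516 = 2,064. This is an upper limit on the calls that item 6 implies and the table omits. It assumes no drop-out, and it does not count calls that would go unmade, because a site could still follow item 6.

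**Are the blanks a reading fault?** The row "Neutralizing Antibody/IgG Test" is ticked at V12 and V13, so those columns were read correctly. The symbols under the visit dates are not shown and might mark the type of contact. They could not create contacts in months that have no column.

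**The case against.** The strongest reply is that follow-up to 12 months is secured in several places, so little is lost.

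- **SAE row.** It carries a single tick under V7, the middle of 13 columns, as do the adverse-event and PCR rows. A footnote allows PCR at any time during the study, so these are probably cells merged across all visits. A reader might infer that SAE collection ends early or is absent at V12 and V13. The table does not support that.
- **Blank telephone cells.** A reader might count V12 and V13 as visits without safety contact. The same row is blank at V4 and V6, which are also blood-draw visits, and section 7.3.2 has adverse events asked about on site. The pattern is not perfect: V8 and V11 are blood draws with a telephone tick, and a parenthesis in 7.3.2 that excepts visits to the research centre muddies its meaning. Still, a blank does not show that no one asks.
- **Medication.** The row "Concomitant Medication" also ends at V11, and a reader might conclude that late events cannot be related to drugs or vaccines. Item 6 does not mention medication, so there is no contradiction with it, and section 7.6 requires medication records to be collected when an SAE occurs.
- **AESI row.** AESIs are adverse events, serious or not, so the lack of a separate row is not an error.
- **Bias.** A certain under-count is not shown. Both arms are blinded, randomised 1:1 and on the same schedule, so any loss is likely to be similar in each.

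These points limit the finding but do not remove it. None of them supplies a contact at months 7, 8, 10 or 11, and item 6 requires one.

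**Conclusion.** Item 6 of section 7.3.1 and the Schedule of Events contradict each other on how SAEs and AESIs are actively sought in the second half of the window for primary endpoint 5. If the schedule is followed, contacts are 90 days apart nominally and up to 120 days at worst, against about 30 days under item 6, and four of the last six months have no contact.

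This is less frequent active ascertainment, not an absence of follow-up. The plausible effects are some missed non-serious AESIs, a change in completeness at month 6, and variation between sites. The absolute 12-month incidence is more exposed than the comparison between arms. The documents give no basis for estimating how many events would be missed.

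The conclusion assumes that the blank cells and missing columns in the schedule are as the sponsor wrote them. It does not depend on how the single tick in the SAE row is read. The documents do not show which of the two plans is intended.

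**What to change.** Reconcile section 7.3.1, item 6, with the Schedule of Events in one of two ways:

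1. Add SAE/AESI telephone contacts at months 7, 8, 10 and 11 to the schedule, and state that SAEs and AESIs are asked about at V12 and V13.
2. If monthly calls after month 6 are not intended, correct item 6 and state that 12-month SAE/AESI incidence rests on 3-monthly contact plus self-report after month 6.

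The first costs a table edit and site time for four short calls per participant, which item 6 already promises. The second costs a sentence or two. Either is best done before participants pass month 6, because contacts not made then cannot be recovered.

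Extending the medication row to V12 and V13, or adding a separate AESI row, is optional and not needed to correct the error.
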